**Visit 4 Final (End of week 18)**

Anthropometric measurement, DEXA scan, OGTT, weight, vital signs, urine for albumin, and blood tests including inflammatory markers will be repeated. Subjects will be asked to complete questionnaires for general health and diet palatability. Subjects will also fast before this visit. Subjects will receive the last ultrasound evaluation at Joslin Diabetes Center and return to HSDM for their fourth dental visit where the final oral examination will be performed and documented.

All subjects, both group (a) and (b), will receive a free dental cleaning at Harvard School of Dental Medicine at Visit 4.

**Detailed Dental Procedures:**

**(**All dental evaluation/ procedures will be performed at Harvard School of Dental Medicine**)**

**Periodontal Examination**

At the **Screening (Visit 1)**, the two HSDM investigators will perform complete periodontal examinations and identifying appropriate sites for GCF to be drawn on all the participants that will include:

1. Hard tissue charting
2. Soft tissue evaluation
3. Probing Depth of pockets utilizing the Florida Probe to standardized periodontal pocket measurements
4. Attachment Loss measurements (CEJ to the depth of the pockets)
5. Mobility measurements
6. Gingival crevicular fluid (GCF) acquisition at 4 sites (mesial-buccal pockets in all first molars) for each patient.

(The GCF will be sent to Boston University Dental School to determine levels of cytokines, IL-1, IL-6, IL-8, and TNF-)

**Full Mouth Dental X-ray Films (Visit 1 ONLY)**

All participants will be seen at the Radiology Department at HSDM for their first visit to obtain a set of full mouth dental x-ray films (16-18 small dental films)

**Periodontal Diagnosis**

The two HSDM investigators will review the physical oral examination data and the full mouth dental x-ray films to arrive at a periodontal diagnosis for each of the fifty participants.

Based on the American Dental Association Classification, the periodontal diagnosis of the fifty participants will be classified into:

Case Type I: Gingivitis

Case Type II: Early Chronic Periodontitis

Case Type III: Moderate Chronic or Aggressive Periodontitis

Case Type IV: Advanced Chronic or Aggressive Periodontitis

Case Type V: Refractory Chronic or Aggressive Periodontitis

Each participant will be informed of their periodontal diagnosis after their first HSDM visit (Baseline data).

After the completion of Visit 1, the participants return to HSDM for their second visit. At the second visit the physical oral examination (Steps 1-6) will be repeated and documented. Data from the second visit will be compared to baseline to ensure no major deterioration in periodontal condition has occurred. If acute periodontal infections occur while the patients are participating in this study, they will be treated at HSDM by the investigators at no charge to the patients.

After the completion of Visit 3, the participants will return to HSDM for the fourth dental visit where the final oral examination, involving Steps 1-6, will be performed and documented.

**Dental Prophylaxis**

At the conclusion of the study, HSDM’s Faculty Group Practice Dental Hygienists will offer all participants a free dental prophylaxis. If they choose this benefit, they will be scheduled for a standard visit with a HSDM dental hygienist.

**Details of Measurements:**

1. **Anthropometric measurements**- measurements of weight, height, waist, hip ratio
2. **Dual Energy X-Ray Absorptiometry (DEXA)**- to evaluate total and regional body fat mass. This measurement will follow standard procedure for body composition measurement and will be performed on Hologic Delphi-A 70372. (Only at End of week 2 (V2), End of 11 (V3), and End of week 18(V4))
3. **Fasting Lipid Panels**- Total cholesterol, HDL, LDL, TG
4. **Hypercoaguability** markers- plasminogen activator inhibitor – 1(PAI-1)
5. **Systolic/Diastolic Blood Pressure**
6. **Insulin Sensitivity** – HOMA-IR, Fasting insulin and glucose level, hemoglobin A1c
7. **Inflammatory markers**- PKC levels in monocytes, CRP, Isoprostane, RNA, IL-6, IL-8, TNF-α, and IL1-.
8. Other **hormones** related to weight and insulin resistance: TSH (Sceening visit only), leptin, adiponectin, ghrelin.
9. **Dental** assessments and collection of GCF to be performed by Harvard School of Dental Medicine.
10. **Vascular functions**: forearm blood flow study by Doppler Ultrasound. Measurement of brachial artery diameter: Flow-mediated endothelium-dependent vasodilatation and endothelium-independent vasodilation will be assessed in the brachial artery using high resolution B-mode ultrasonography. An ultrasound scanner (Toshiba model SSH-140A) equipped with a high-resolution linear array transducer (7.5 mHz) will be used to image the brachial artery and thus enable measurement of its diameter and cross-sectional area. A longitudinal image (parallel to the artery) will be acquired just proximal to the antecubital fossa. The transducer will be positioned at 90 degrees to the vessel to acquire an image through the center line of the vessels so that the near and far wall interfaces will be clearly discernible. A simultaneous electrocardiographic signal will be recorded. The video output and electrocardiographic signal of the ultrasound machine will be connected to a computer equipped with a Data Translation frame grabber video card. The R wave on the electrocardiogram will be used as a trigger to acquire (digitize) frames. Digitized images at baseline and after intervention (e.g., reactive hyperemia, nitroglycerin) will be stored on the hard drive and backed up on removable media. Acquisition and analysis of the stored images will be performed using software designed for this purpose by Information Integrity, Inc. The vessel wall lumen interface is determined by derivative based edge detection following identification of the region of the anterior and posterior walls by the investigator. The maximum diameter of the vessel is then determined. This technique yields an interobserver variability of 0.05±0.16% and intraobserver variability of 0±0.15%.

This study will be performed at the Joslin Diabetes Center. The dental evaluation will be performed with investigators from Harvard School of Dental Medicine.

###### Study Procedures Flow Sheet

| **Study Visits** | **Procedures Checklist** |
| --- | --- |
| **Visit 1**  **Screening** (Wk 0-2)    Beginning of Week 0  About 5 hours | - *Complete Initial screening form and Dental screening form   (before the Visit 1)   - Fasting before Visit   (No food, no drink, except water for 10 hours before visit)   - Meet with **Physician** for   **- Collect the Joslin Diabetes Center Consent Form**  - Initial screening  - Explanation of the study   - Meet with **Nurse** for   - Vital Signs  - OGTT – test for diabetes  - Pregnancy test for women by obtaining a urine sample  - Blood draw   - Meet with **Dietician** for   - Measurements of weight, height, hip, and waist  - Nutrition assessment, discussion of intervention diets  - Discuss physical activity (PA),  - Ascertain history of food allergies   - Meet with **Investigator at HSDM** for   - Explaining dental procedures  **- Obtaining HSDM Consent Form**  - Full mouth dental x-ray   - * Complete General Health Questionnaire 1 - Free Parking as needed |
| **Visit 2**  **Asian Diets** for both Intervention **(b)** & Control **(a)**  (Wk 2-10)    End of Week 2  About 5 hours | - Fasting before visit   (No food, no drink, except water for 10 hours before visit)   - Meet with **Nurse** for   - Vital Signs  - Urine Protein test by obtaining a urine sample  - Blood draw – lipids, inflammatory markers   - Meet with **Dietician** for   - Measurements of weight, height, hip, and waist  - DEXA scan (to determine percentage of body fat)   - Meet with **Investigator at HSDM** for:   - Dental evaluation   - Compensation: $50.00 after completing this visit - Free Parking as needed - Forearm blood flow measurement (Doppler Sonography Ultrasound) - Randomization occurs at the end of week 10 |
| **Visit 3**  **WD** for intervention group  **AD** for control group  (Wk 10-18)  End of Week 10  About 5 hours | - Fasting before visit   (No food, no drink, except water for 10 hours before visit)   - Complete General Health Questionnaire 2 - Meet with **Dietician** for   - Measurements of weight, height, hip, and waist  - DEXA scan (to determine percentage of body fat)   - Meet with **Nurse** for   - Vital Signs  - OGTT – test for diabetes  - Urine Protein test by obtaining a urine sample  - Blood draw – lipids, inflammatory markers   - Meet with **Investigator at HSDM** for:   - Dental evaluation   - Compensation: $150.00 after completing this visit - Free Parking as needed - Forearm blood flow measurement (Doppler Sonography Ultrasound) - Complete Diet Palatability Survey |
| **Visit 4**  Final Visit  End of Week 18  Total Hours: About 5 hrs | - Fasting before visit   (No food, no drink, except water for 10 hours before visit)   - *Complete General Health Questionnaire 3 - *Complete Diet Palatability Survey - Meet with **Dietician** for   - Measurements of weight, height, hip, and waist  - DEXA scan (to determine percentage of body fat)   - Meet with **Nurse** for   - Vital Signs  - OGTT – test for diabetes  - Urine Protein test by obtaining a urine sample  - Blood draw – lipids, inflammatory markers   - Meet with **Investigator at HSDM** for:   - Dental evaluation  - Free dental cleaning for all subjects (both group **(a)** and **(b)**)   - Compensation: $300.00 after completing this visit - Free Parking as needed - Bilingual Guide – Staying Healthy with Diabetes - Forearm blood flow measurement (Doppler Sonography Ultrasound) |

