**Details of Study Procedure(s)**

**Visit 1 – Screening (Week 0 – Week 2)**

Prior to Visit #1, all subjects will be screened by a checklist (base on inclusion/exclusion criteria listed in Part C). Each will be asked to fast before coming to the visit.

Eligible subjects will be scheduled for **Visit 1 (beginning of week 0)** with a study physician who will collect the consent forms from Joslin Diabetes Center and Beth Israel Deaconess Medical Center. Medical history, physical examination, anthropometric measurements, blood tests, blood pressure, pregnancy tests for females, and an oral glucose tolerance test will be performed after this. Those who have blood glucose results > 200mg/dl from oral glucose tolerance test will be excluded from the study. A registered dietician will perform a 24-hour diet recall, counsel the dietary procedures and use of accelerometer. Total Energy Expenditure (TEE) for each subject will be calculated to determine caloric intake using the following equation:

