**Visit 3 - WD or AD (Week 11 – 18)**

At Visit 3 (End of Week 10), all subjects will receive an envelope that will determine if subjects will be randomized to the control (continue another 8 weeks of Asian Diets) or the intervention group (switching to 8 weeks of Western Diets). Anthropometric measurement, DEXA scan, weight, OGTT, vital signs, and blood tests including inflammatory markers will be repeated. Requirements in this phase will be the same as Visit 2. Subjects will be asked to complete a questionnaire about General health and quality of life. All subjects will also complete a Diet Palatability Survey, receive a forearm ultrasound evaluation at Joslin Diabetes Center and dental examination at HSDM. All subjects will fast before coming to this visit. While the **Control group(a)** will continue on AD, the **Intervention group(b)** will switch from AD to 8 weeks of WD prepared and packed by Veronique Corporation. starting from this visit.

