###### *Please see appendix 3 for questionnaires and screening forms

###### INCLUSION / EXCLUSION CRITERIA

**Inclusion criteria:**

1. Caucasian or Far-East Asian decent
2. Ages between 25 – 55 years old
3. Has family history of diabetes defined as having a first degree relative diagnosed with diabetes mellitus and/or medical history of gestational diabetes (GDM), impaired fasting glucose (IFG) and impaired glucose tolerance (IGT)
4. BMI of 18.5 – 27.0 kg/m2
5. Agree to maintain constant physical activity levels for the duration of the study
6. Agree to utilize contraception for the duration of the study (for female subjects)
7. Have a minimum of 12 natural teeth
8. Scoring of 2 or more on dental screening questionnaire (See appendix)
9. Ability to communicate in English.

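### The only scheduled pregnancy test is at Visit 1, so its result is about 10 and 18 weeks old at the Visit 3 and Visit 4 DEXA scans: a minor safety gap with a cheap fix

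*Protocol*

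**What the plan says.** Pregnancy is an exclusion (Exclusion criteria, item 9). Inclusion criterion 6 extends the concern to the whole study: "Agree to utilize contraception for the duration of the study (for female subjects".

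Testing appears at one visit only. The Visit 1 narrative includes "pregnancy tests for females, and an oral glucose tolerance test will be performed after this", and the Visit 1 row of the Study Procedures Flow Sheet lists "Pregnancy test for women by obtaining a urine sample". Visit 1 falls at the beginning of week 0.

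DEXA comes later and is repeated:

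- Details of Measurements gives the timing as "Only at End of week 2 (V2), End of 11 (V3), and End of week 18(V4".
- The Visit 3 narrative reads "Anthropometric measurement, DEXA scan, weight, OGTT, vital signs, and blood tests including inflammatory markers will be repeated".
- The Visit 4 narrative reads "Anthropometric measurement, DEXA scan, OGTT, weight, vital signs, urine for albumin, and blood tests including inflammatory markers will be repeated".

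Neither of those narratives, nor the matching flow-sheet rows, lists a pregnancy test. The flow sheet does collect urine at Visits 3 and 4, for another purpose: "Urine Protein test by obtaining a urine sample". On how the scan is done, Details of Measurements says only: "This measurement will follow standard procedure for body composition measurement". The DEXA Scan paragraph under Possible Risks acknowledges low-level radiation and puts the dose below 5 percent of one year's natural background.

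**The concern.** The protocol treats pregnancy as a matter for the full 18 weeks but checks it by test only at entry. A woman who conceives after week 0 and has not recognised it could have DEXA at Visit 3, Visit 4 or both without a current result. The visit schedule belongs in the protocol, so a statistical analysis plan that is not shown would not be expected to settle this.

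The other controls lower the risk but are not tests. Women agree to use contraception. Under Details of the Intervention Group(s), subjects are weighed every two weeks and telephoned weekly by a dietitian, which gives them chances to report a pregnancy. The section on omitting procedures or leaving the study covers only the subject's own decision. The text shown gives staff no instruction for a pregnancy found during the study.

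What is at stake is an avoidable, low-dose exposure in a small number of women.

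**Working it through.** **Timeline.** Run-in is 2 weeks and the two diet periods are 8 weeks each (Study Design): 2 + 8 = week 10 for Visit 3, and 10 + 8 = week 18 for Visit 4. This reproduces the stated 18-week length.

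**Age of the test at each scan** (week of scan minus week 0).

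- Visit 2: 2 − 0 = 2 weeks
- Visit 3: 10 − 0 = 10 weeks (11 if the week in Details of Measurements is used; the Visit 3 narrative and flow sheet say the end of week 10)
- Visit 4: 18 − 0 = 18 weeks

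**Expected number of cases.** The protocol gives no conception rate, so the following are assumptions with ranges.

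- W, women enrolled: 25 or 35, half of the two sample sizes that Study Design implies (50, or 35 per ethnic group = 70). Recruitment is said to seek both sexes equally.
- f, share able to conceive: 0.75 (0.5 to 1; the age limit is 55)
- p, conceptions per woman-year despite contraception: 0.03 (0.01 to 0.10)
- L, weeks from conception to a positive urine test: 3 (2 to 4)
- r, share recognised and reported without a test: 0.5 (0 to 0.75)

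Pregnancies over the study = W × f × p × 18/52.

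- W = 25: 25 × 0.75 × 0.03 × 18/52 = 0.19
- W = 35: 35 × 0.75 × 0.03 × 18/52 = 0.27

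Pregnancies newly identified by tests at Visits 3 and 4, each counted once = W × f × p/52 × (18 − L) × (1 − r).

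- W = 25: 25 × 0.75 × 0.03/52 × 15 × 0.5 = 0.08
- W = 35: 35 × 0.75 × 0.03/52 × 15 × 0.5 = 0.11

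Untested scans affected. A woman who conceives early enough could be scanned at both visits, so the bracket becomes (10 − L) + (18 − L) = 7 + 15 = 22.

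- W = 25: 25 × 0.75 × 0.03/52 × 22 × 0.5 = 0.12
- W = 35: 35 × 0.75 × 0.03/52 × 22 × 0.5 = 0.17

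**Sensitivity.** Varying one assumption at a time for newly identified pregnancies, W = 25, mid case 0.081:

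| Assumption varied | Range | Result |
| --- | --- | --- |
| p | 0.01 to 0.10 | 0.027 to 0.270 |
| r | 0.75 to 0 | 0.041 to 0.162 |
| f | 0.5 to 1 | 0.054 to 0.108 |
| L | 4 to 2 | 0.076 to 0.087 |

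For W = 35, multiply by 35/25 = 1.4; the largest entry becomes 0.270 × 1.4 = 0.38. All are well under one.

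**Visit 2.** With L of 2 to 4 weeks, a test at week 2 would not detect a conception after week 0, since 2 − L is zero or negative. A repeat there adds little.

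**Dose.** If the 5 percent bound is per scan, the scans at Visits 3 and 4 together stay below 2 × 5 = 10 percent of one year's natural background.

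**The case against.** The strongest reply is that nothing here is contradictory. Pregnancy is an entry exclusion and is tested at entry; the later weeks are covered by a different control, contraception. On that view a repeat test is a preference. The internal consistency is granted, which is why the point is offered as an improvement to the schedule and not as an error.

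A second reply is that a check may exist out of view. General Health Questionnaires 2 and 3 are completed at Visits 3 and 4, their content is in an appendix not shown, and DEXA follows a standard procedure that is not reproduced. Consent pages were removed before review. Any of these could contain a pregnancy question. This stands, so the point is limited to scheduled tests. A reader might infer that women are scanned with no check at all; the documents do not establish that.

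A third reply concerns size. Every input beyond the visit weeks and the sample size is assumed. A reader who set all assumptions to their extremes together could reach more than one affected scan. That would require pregnancies to go unrecognised for up to 18 weeks despite fortnightly weighing and weekly calls, and it should not be used.

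Two further inferences also fail. One is that the ultrasound with nitroglycerin should be withheld as well: the protocol does not name pregnancy as a nitroglycerin hazard. The other is that the gap affects the PKC comparison: nothing in the documents suggests it does.

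**Conclusion.** The point holds as a minor participant-safety improvement. The ages of the test at the scans, about 10 weeks (or 11) and 18 weeks, follow directly from the protocol's schedule and rest on no assumption.

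The number of women affected does rest on assumptions and is small: about 0.08 to 0.11 newly identified pregnancies in the mid case, and no more than about 0.4 when any single assumption is moved to its limit. The stated dose is low. The case for acting is that the remedy costs very little and the protocol already treats pregnancy as a concern for the whole study. The case weakens further if the DEXA procedure or the questionnaires already include a check.

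**What to change.** In the Study Procedures Flow Sheet, add to Visits 3 and 4 a urine pregnancy test for women who can conceive, using the urine already collected for the protein test, and state that it is read before DEXA. If it is positive, withhold DEXA and refer the subject to the study physician. Make the same addition to the Visit 3 and Visit 4 narratives; the Visit 3 narrative does not currently mention urine, although the flow sheet does.

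Cost: two dipsticks per woman who can conceive. With 25 women and a share of 0.5 to 1, that is 13 × 2 = 26 to 25 × 2 = 50 in total; with 35 women, 18 × 2 = 36 to 35 × 2 = 70. No new visit or sample is needed. The one practical downside is order: at both visits the flow sheet lists the dietitian's DEXA before the nurse's urine collection, so urine must be collected and read first. If the local DEXA procedure already requires a pregnancy test, the protocol need only say so.

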###### *Please see appendix 3 for questionnaires and screening forms

###### INCLUSION / EXCLUSION CRITERIA

**Inclusion criteria:**

1. Caucasian or Far-East Asian decent
2. Ages between 25 – 55 years old
3. Has family history of diabetes defined as having a first degree relative diagnosed with diabetes mellitus and/or medical history of gestational diabetes (GDM), impaired fasting glucose (IFG) and impaired glucose tolerance (IGT)
4. BMI of 18.5 – 27.0 kg/m2
5. Agree to maintain constant physical activity levels for the duration of the study
6. Agree to utilize contraception for the duration of the study (for female subjects)
7. Have a minimum of 12 natural teeth
8. Scoring of 2 or more on dental screening questionnaire (See appendix)
9. Ability to communicate in English.

**Exclusion criteria:**

1. Acute weight loss/weight gain over the past 6 months (defined as +4 lbs or more/month)
2. History of diabetes
3. Current Smokers (including those who quit < 1 year)
4. Heavy alcohol drinkers, defined as drinking more than 7 drinks/week. Those who drink alcohol will need to be reported and documented. They will be asked to maintain the levels of alcohol consumption throughout the study.
5. Medical history of vascular diseases (CAD, MI, stroke, CABG, angioplasty), diabetes, liver disease, kidney disease, cancer, AIDS, bleeding disorders
6. History of food allergies or to any food products in the diet menu
7. Enrolled in another investigational study within 1 month prior to screening for this study
8. Vegetarian, those with significant food aversions, and anyone who cannot comply with the diet
9. Pregnancy or breasting feeding
10. Other autoimmune or inflammatory conditions or diseases that may compromise the patient's safety or compliance during the study on an individual basis
11. Chronic use of antibiotics or anti-inflammatory medications (>1 month) within the past year
12. On medications such as statins, angiotensin converting enzyme inhibitor, warfarin, aspirin or other anti-inflammatory medications. Daily multivitamins are permitted, excluding pharmacological doses of anti-oxidants will not be allowed.
13. *Individuals with dental needs requiring extensive dental restorations such as cavities, root canals, crowns, etc.*

## **Details of Outcome Measurements**

## OGTT, laboratory analysis of blood and screening for medical history will be performed to exclude patients with diabetes mellitus, food allergies and other chronic illnesses that will prevent them from participating safely in the study. OGTT, laboratory tests for inflammatory markers, lipids, glucose, thyroid functions, DEXA scan, forearm Doppler Sonography, and dental evaluation will be performed at baseline and measure outcomes of each diet phase. Questionnaires will also be used to assess subjects’ view of health status pre and post interventions. See study flow sheet above for types and frequency of measurements performed throughout the study.

###### DATA ANALYSIS / SUBJECT SELECTION

**Statistical Considerations**:

**Sample size and power calculations**:

This study is a pilot/ feasibility study. The primary hypothesis of this study is to compare changes in PKC activity due to the transition from a traditional Asian diet to a typical American diet in two different ethnic groups, Asian and Caucasian. The interest is the mean percent change in marker levels between the two ethnic groups, which would be the values at timepoint 3 (after exposure to American diet) minus the values at timepoint 2, divided by the measure at time point 2 times 100. This would give the percent change that could be accounted for by exposure to the different diets in each ethnic group. For this comparison, the power for comparing the net change between the two ethnic groups of 20 individuals who will change from a traditional Asian diet to an American diet was calculated. Additionally, two control groups (one of each ethnicity) will remain on the traditional Asian diet as a control for potential outside effects on the primary hypothesis, the power calculations for comparing the control group to the active group can also be found below.

A total of 25 individuals of each ethnic group will be randomized into either the traditional Asian diet group (n=5) for each period or into the traditional diet and then the American diet (n = 20). The total number of participants is limited by cost. It is our hope that the 5-person control arms makes it possible to assess whether a factor outside of diet contributed to any differences observed. These control groups of ten will only be used for a subset analysis to get an idea of possible environmental effects on the outcome of interest, change in PKC activity. An appropriate two-sample test will be used for this determination, with the alpha and power given in the proceeding paragraph.

The power for the examination of percent change in PKC activity, the primary hypothesis, was calculated using STATA 7.0 (College Station, Texas 2001). An assumption of a one-sided test with an alpha of 0.05 was made. Mean PKC measurements were estimated at 78.1*[[6]](#endnote-7)* ±5 (there is no expected ethnic variation in PKC activity levels). Calculations are based on change exhibited by cardiac cells with exposure to increased lipids. In previous trials a 50% change has been observed in PKC activity in the cytosol of cardiac cells.

Table 1. Power calculations for PKC activity percent change to detect a difference between Caucasian and Asian American groups when exposed to the American diet.

| **Size of Group 1** | **Size of Group 2** | **Percent change** | **PKC estimate** | **PKC Std dev (+)** | **Power** |
| --- | --- | --- | --- | --- | --- |
| 25 | 25 | 10 | 85.91 | 5.5 | 0.999 |
| 25 | 25 | 5 | 82.005 | 5.25 | 0.8527 |

This summary table of power to detect a significant difference suggests that a study using this approach would have adequate power to detect a difference between the two groups in PKC activity. We do not expect to see a difference less than 5%.

Table 2.  Power calculations for PKC activity change with change in diet based on a comparison to detect a difference between the control group and those exposed to the American diet. The baseline PKC activity value used in this calculation is 78.1 5.

| **Size of Group 1** | **Size of Group 2** | **Percent change** | **Comparison values** | **Power** |
| --- | --- | --- | --- | --- |
| 10 | 25 | 10 | 85.91 5.5 | 0.969 |
| 10 | 25 | 5 | 82.005 5.25 | 0.875 |

This demonstrates that we have adequate power to detect as low as a 5% change between the two groups. This exceeds our needs as estimated change is approximately 50%.

In addition to the primary endpoint of change in PKC levels, changes in Flow Mediated Dilation (FMD) and CRP are of interest. These differences will be examined by two-sample tests, either two-sample t or Wilcoxon sign rank. The power curves based on current literature for changes in FMD can be found below, based on a one-sided hypothesis using an alpha of 0.05, for the detectable difference of percent change between ethnic groups. The power to detect a difference in percent change for CRP measures was also examined. Our estimates indicate that there is insufficient power (~50%) to detect a difference as large as 25 between the two percent change measures. This was calculated assuming a one-sided test with an alpha of 0.05.

 Additionally, we present the power curve for the detection of difference in percent change in Flow Mediated Dilation.

Figure 1. Power curve for percent difference in FMD between Caucasians and Asians (the x-axis represents difference between the two measures) [[7]](#endnote-8),[[8]](#endnote-9) ,[[9]](#endnote-10),[[10]](#endnote-11)

From this graph it is evident that there will be sufficient power to detect a difference in FMD change between the two groups. [[11]](#endnote-12),[[12]](#endnote-13)

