**Data Analysis:**

Our primary a priori hypothesis is to detect if there is a difference in PKC activity change between Caucasians and Asians with exposure to American diets, which will be done through a two-sample test (either t-test or Wilcoxon signed-rank sum, depending on distribution). A secondary hypothesis is to examine the difference in change of Flow Mediated Dilation before and after exposure to the American diets between the two ethnic groups, which will also be examined through a two-sample test. These will be examined with an alpha set at 0.05. Additionally, we expect to do several exploratory analyses, including anthropometrics, lipids, fibrinogen, IL-6, TNF-alpha, E-selectin, Isoprostane, Fox II, leptin, adiponectin, and ghrelin. We will use Scheffé’s procedure for linear contrasts, as the comparison of means is a special case of this to help correct for multiple comparisons. However, correction for multiple comparisons will be applied for all exploratory hypotheses.

Multiple potential confounding variables will be controlled for by including limitations on age, family history of diabetes, limited range of BMI (estimated body fat content), and physical activity. We will also take a diet history and exclude those with medical illnesses. These steps will not exclude all bias but should limit it in this study. The potential role of effect-modifiers will also be considered in the interpretation of the data. A preliminary stratified examination will be done to determine if there is a significant difference between exposed and unexposed groups of the same ethnicity. Baseline and post intervention measures permits change from baseline analysis. If change from baseline differs between groups, we are interested in designing future studies to identify the factors that mediate the differences in response between ethnic groups.

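### Table 1's 0.8527 is the power of a one-sided test on PKC levels, whereas the primary hypothesis is a non-directional difference in percent change

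*Protocol*

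**What the plan says.** The sample size section defines the primary quantity: "The interest is the mean percent change in marker levels between the two ethnic groups", computed as the timepoint 3 value "minus the values at timepoint 2, divided by the measure at time point 2 times 100". The primary endpoint is therefore a within-subject percent change, compared between Asian and Caucasian subjects who switch diet.

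For power, the same section states "An assumption of a one-sided test with an alpha of 0.05 was made" and gives the input as a level: "Mean PKC measurements were estimated at 78.1", with a spread of 5 and no ethnic variation expected. Table 1, captioned as power for percent change between the ethnic groups, lists 25 per group, a PKC estimate of 82.005 with SD 5.25 for a 5% change, and power 0.8527. For a 10% change it lists 85.91, SD 5.5 and power 0.999. The protocol concludes that power is adequate and that no difference smaller than 5% is expected.

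The Data Analysis section words the hypothesis without direction: "Our primary a priori hypothesis is to detect if there is a difference in PKC activity change between Caucasians and Asians". On the error rate it says only "These will be examined with an alpha set at 0.05", without sidedness.

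**The concern.** A power figure describes a test only if it uses that test's sidedness and the variance of its endpoint. Table 1 departs from the stated hypothesis on both.

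- **Sidedness.** A one-sided test needs a direction. The protocol never says which ethnic group should change more.
- **Variance.** The SD of a percent change depends on how strongly a subject's two PKC values correlate. Table 1 uses the between-subject SD of single levels, and the protocol gives nothing from which the SD of percent change could be derived.

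At stake is the claim of adequate power at 5%, the smallest difference the protocol expects. A reader who takes 0.85 as the power of the primary comparison relies on a figure for another test.

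**Working it through.** **Inputs from the protocol.** Means 78.1 and 82.005 (= 78.1 × 1.05); SDs 5 and 5.25; one-sided alpha 0.05; 25 per group (Table 1); 20 per group (sample size section, for the same comparison). **Assumed, because not given:** within-subject correlation r from 0 to 0.9.

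**1. Reproducing the stated figure.** Power = Φ(difference / SE − z).
- Difference = 82.005 − 78.1 = 3.905.
- SE = √(5²/25 + 5.25²/25) = √2.1025 = 1.45.
- 3.905/1.45 = 2.693, and Φ(2.693 − 1.645) = **0.8527**, the printed value to four decimals.

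The 10% row gives 0.9998 against the stated 0.999. The table is thus a one-sided z test on two independent mean levels.

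**2. Sidedness alone, 25 per group.** Φ(2.693 − 1.960) = **0.77** (noncentral t: 0.75).

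**3. Group size, kept separate.** With 20 per group, SE = √(52.5625/20) = 1.621 and 3.905/1.621 = 2.409.
- One-sided: Φ(2.409 − 1.645) = **0.78**.
- Two-sided: Φ(2.409 − 1.960) = **0.67** (noncentral t: 0.65).

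The fall from 0.85 to 0.67 therefore has two sources of similar size. Only one of them is sidedness.

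**4. The endpoint as defined.** Compare a mean change of 0% with one of 5%. Let the SD scale with the mean, as in Table 1, so that the coefficient of variation is c = 5/78.1 = 6.4% at both visits. To first order, where f is the ratio of the later mean to the earlier one (1 or 1.05),

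SD of percent change ≈ 100 · f · c · √(2(1 − r)).

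Two-sided power for a 5-point difference, 20 per group:

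| Assumed r | SD, 0% group | SD, 5% group | Power, z with these SDs | Power, noncentral t with simulated SDs |
|---|---|---|---|---|
| 0 | 9.05 | 9.51 | 0.40 | 0.38 |
| 0.5 | 6.40 | 6.72 | 0.67 | 0.64 |
| 0.7 | 4.96 | 5.21 | 0.87 | 0.85 |
| 0.9 | 2.86 | 3.01 | above 0.99 | above 0.99 |

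The simulated SDs are slightly larger than the first-order ones (for example 9.2 and 9.6 at r = 0). At r = 0.5 the factor √(2(1 − r)) equals 1, so the levels and percent-change calculations coincide to first order. Below 0.5 the levels calculation overstates power, and above it understates.

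**5. What the 5% means.** Table 1's 5% is a ratio of means. If both groups also rise by about half, the same ratio gives 50% against 57.5% (1.5 × 1.05 = 1.575). Difference and SDs both grow by 1.5, so the powers in step 4 are unchanged. Read instead as 5 additive points, 50% against 55%, power is about 0.20, 0.35 and 0.94 at r = 0, 0.5 and 0.9. The protocol does not say which reading it intends.

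**The case against.** The arithmetic of 0.8527 is right for its own inputs. The protocol never says two-sided, and its power section assumes one-sided tests consistently, for PKC, FMD and CRP. Further detail of the test could sit in a statistical analysis plan. The study calls itself a cost-limited pilot, and at a 10% difference with 20 per group, two-sided, power is 0.997 on levels and 0.89 on percent change even at r = 0. All of this stands. It limits the consequence, but it supplies neither the missing direction nor the missing variance behind a figure that the protocol itself prints.

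Four stronger readings are tempting and not supported:

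- **That true power is well below 0.85.** At r = 0.7 it equals 0.85 and at r = 0.9 it exceeds 0.99. Power is undetermined, not shown to be low.
- **That sidedness takes 0.85 to 0.67.** Sidedness alone gives 0.77. The rest comes from 25 against 20 per group.
- **That the error rate is 10%.** That needs a direction chosen after seeing the data, and no section plans this.
- **That the 50% diet effect is used to justify the ethnic contrast.** The sentence "This exceeds our needs as estimated change is approximately 50" percent follows Table 2, which compares controls with subjects on the American diet, where a diet effect is the relevant quantity. What remains is looser: the sample size section says the calculations rest on the cardiac-cell change, without saying that this is a diet effect and not an expected ethnic difference.

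**Conclusion.** The point holds as a mismatch between a printed power and the planned comparison. The 0.8527 belongs to a one-sided test on levels, while the hypothesis is non-directional and concerns percent change. Correcting sidedness alone lowers the figure by 0.08 (0.85 to 0.77) at Table 1's own group size. Correcting the endpoint leaves power anywhere from about 0.38 to above 0.99 with 20 per group, depending on a correlation that the protocol does not give. That range assumes 0% against 5% change, SDs proportional to the mean, and r between 0 and 0.9. The conclusion of adequate power at 5% is therefore unsupported as written, though not shown to be false.

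**What to change.** - State the primary test as two-sided at 0.05, or name in advance the ethnic group expected to change more, and why.
- Recompute Table 1 for the difference in mean percent change at 20 per group, the number the sample size section gives for this comparison. Reconcile that number with the 25 in Table 1 and in the Study Design text. Use an SD of percent change over a stated range of within-subject correlations, and say whether the 5% is additive or multiplicative.
- Restate the conclusion about adequate power to match the new table.
- Keep the 50% sentence after Table 2, but confine it to the control-versus-diet contrast. In the sample size section, say that the 50% cardiac-cell change is a diet effect and not the expected ethnic difference.

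Cost: protocol wording and one recomputed table. The stated power may fall. No extra subjects are needed.
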